## Abstract

**Introduction:**

Individuals of recent West African ancestry develop focal segmental glomerulosclerosis (FSGS) and hypertension-attributed end-stage kidney disease (HTN-ESKD) at 4 times the rate of White Americans. Two protein-coding variants of the Apolipoprotein L1 (APOL1) gene, G1 and G2, explain 50% to 70% of the excess risk of HTN-ESKD and FSGS among this group. Increased expression of G1 and G2 in the kidney, mediated by Janus kinase/signal transducer and activator of transcription (JAK-STAT) signaling, drive pathogenesis of these kidney diseases. Baricitinib is an orally active inhibitor of JAK1/2 that blocks APOL1 synthesis. The Janus kinase-STAT Inhibition to Reduce APOL1-Associated Kidney Disease (JUSTICE) trial is evaluating the antiproteinuric efficacy and safety of baricitinib in patients with APOL1-associated FSGS and HTN-attributed chronic kidney disease (HTN-CKD).

**Methods:**

JUSTICE is a single-center, randomized, double-blind, placebo-controlled, pilot phase 2 trial of baricitinib in patients with proteinuria, APOL1-associated FSGS or APOL1-associated HTN-CKD without diabetes. A total of 75 African American patients with APOL1-associated CKD, including 25 with FSGS and 50 with HTN-CKD, aged 18 to 70 years will be randomized 2:1 to daily treatment with baricitinib or placebo, respectively.

**Results:**

The primary efficacy end point will be percent change in urine albumin-to-creatinine ratio (UACR) from baseline to end of month 6. The primary safety end point will be incidence of clinically significant decreases in hemoglobin of ≥ 1g/dl.

**Conclusion:**

The phase 2 JUSTICE study will characterize the antiproteinuric efficacy and safety of JAK1/2 inhibition with baricitinib in patients with APOL1-associated FSGS and APOL1-associated HTN-CKD.

Among African Americans and other individuals of recent West African ancestry, FSGS is the leading cause of nondiabetic nephrotic syndrome, and HTN-CKD is the leading cause of ESKD not due to diabetes.^1^ Although social and structural determinants of health, including racism, poverty, discrimination, and lack of access to health care contribute to racial inequities in kidney health,^2^ 2 protein-coding variants of the gene apolipoprotein L1 (APOL1), G1 and G2, found exclusively in individuals of recent West African ancestry, account for much of the excess risk of FSGS and HTN-ESKD in African Americans.^3^ Approximately 13% of African Americans carry 2 risk variants of APOL1 (G1G1, G2G2, or G1G2), collectively referred to as high-risk genotypes (HRGs). By comparison, 70% of African Americans with FSGS and 40% with HTN-ESKD carry HRGs. Compared to African Americans with low-risk APOL1 genotypes (G0G0, G0G1, and G0G2), APOL1 HRGs increase the risk of FSGS 17-fold and HTN-ESKD up to 11-fold.^3^^,^^4^ Significant progress in understanding the pathomechanism of APOL1-mediated kidney disease (AMKD) has yielded promising therapeutic candidates; however, there is currently no FDA-approved drug for APOL1-associated kidney disease.^5^, ^6^, ^7^, ^8^ The use of nonspecific immunosuppressants for APOL1-associated FSGS and antihypertensives for APOL1-associated HTN-CKD fail to slow the rapid progression of these common forms of kidney disease to ESKD.^4^^,^^9^ There is an unmet need for specific therapy for AMKD.

Proteinuria and glomerular sclerosis, which are clinical and histopathologic consequences of sustained podocyte injury, are hallmarks of AMKD.^10^, ^11^, ^12^ Podocyte injury and subsequent proteinuria, with a 3-fold higher incidence in carriers of APOL1 HRG are the early clinical manifestations of AMKD.^11^^,^^12^ We and others have demonstrated that transgenic expression of APOL1 G1 or G2 in podocytes of zebrafish^13^ and mice^6^^,^^8^^,^^14^ is sufficient to cause podocyte injury, glomerular sclerosis, and proteinuria. Furthermore, inhibition of APOL1 expression by antisense oligonucleotides ameliorated podocyte injury and proteinuria in APOL1 transgenic mice.^14^ By comparison, expression of the reference APOL1 allele, G0, in mouse podocytes or tubular cells was nontoxic.^6^ Together, these results indicate that increased expression of APOL1 risk variants cause CKD via podocyte injury.

Observation that only 15% to 20% of carriers of HRG develop AMKD^15^ suggests that “second hits” are required to induce CKD in high-risk individuals. Two types of second hits have been identified as triggers of APOL1-mediated FSGS. First, elevated interferon states due to iatrogenic exposure,^16^ genetic mutations, such as TMEM173 (SAVI), which boosts synthesis and endogenous release of interferon,^17^ or disease processes such as systemic lupus which increase systemic interferons levels.^18^ Second, viral infections, especially HIV^4^^,^^19^ and most recently, COVID-19^20^ can cause collapsing glomerulopathy in African American carriers of 2 APOL1 risk variants. Experimental evidence suggests that COVID-19 causes collapsing FSGS by increasing systemic inflammatory cytokines, which in turn synergistically increase the expression of pathogenic APOL1 renal risk variants in podocytes and glomerular endothelial cells.^21^

JAK-STAT signaling is the common pathway that mediates the effect of interferons and noninterferon cytokines, including TNF-α, IL-6 and IL-1β, in inducing renal APOL1 expression.^21^^,^^22^ Inhibition of JAK1/2 effectively blocks APOL1 expression in human primary podocytes and glomerular endothelial cells.^21^ Importantly, our preliminary study shows that the JAK-STAT signaling pathway is potentiated in podocytes derived from patients with FSGS who carried HRG compared to podocytes from African Americans with HRG who are free of kidney disease.

The high population attributable risk of HTN-ESKD supports its causal link to pathogenic APOL1 variants;^15^ however, the second-hit trigger of APOL1-mediated pathogenesis of HTN-CKD is unknown. Induced expression of APOL1 risk variants in mice caused kidney failure without causing HTN.^8^ In patients with APOL1 HRG, antihypertensive medication did not slow the progression of HTN-CKD to ESKD.^9^ Together, this evidence suggests that HTN *per se* is less likely to be the second-hit trigger of APOL1-mediated HTN-CKD, but rather a consequence of it. We hypothesize that the inflammatory cytokines, including TNF-α, IL-6 and IL-1β, known to be elevated in patients with HTN, likely induce the expression of pathogenic APOL1 via JAK-STAT signaling, thereby contributing to the pathogenesis of APOL1-mediated, HTN-CKD.^23^, ^24^, ^25^, ^26^ Therefore, we hypothesize that clinically available inhibitors of JAK1/2 will block kidney APOL1 expression and thereby slow the progression of APOL1-mediated HTN-CKD.

JAK-STAT signaling is a ubiquitous pathway that contributes to erythropoiesis. Because baricitinib inhibits JAK2-mediated, erythropoietin-induced erythrocytosis, anemia is a potential side effect of baricitinib. However, data from 8 randomized clinical trials involving a total of 3492 participants and 7993 total person-years of exposure reported only a marginal reduction of −0.12 mmol/l in hemoglobin of patients receiving baricitinib.^27^ Moreover, previous trials in which baricitinib was used in patients with diabetic kidney disease did not show increased incidence of anemia or other hematologic abnormalities.^28^

The randomized, double-blind, placebo-controlled, pilot phase 2 JUSTICE trial has been initiated to study the efficacy and safety of baricitinib, a JAK1/2-specific inhibitor, in reducing proteinuria in patients with APOL1-associated FSGS or HTN-CKD over a period of 6 months. This paper describes the study design and methodology of the JUSTICE trial.

African Americans, who are overrepresented in advanced stage CKD and glomerulonephritis, are underrepresented in therapeutic trials in CKD accounting for 18% and 12%, respectively compared to 57% and 37% for White patients.^29^ Multiple barriers summarized in Table 1 account for this underrepresentation.^30^^,^^31^ To address these barriers, we established the Community APOL1 Research Engagement (CARE) registry (www.kidneycareandjustice.com) through which we engage, inform, and screen African Americans and other self-identified Black people in the United States of America for AMKD. By facilitating efficient identification of African Americans who are potentially eligible for the JUSTICE trial, the CARE registry will increase the enrolment of African Americans in this trial.

**Table 1 tbl1:** Common barriers to participation in clinical trials and strategies employed by the CARE and JUSTICE studies aimed to reduce them

Key barriers to African American participation in clinical trials	Strategies for addressing key barriers in CARE and JUSTICE
1. Lack of kidney disease awareness.	Accessible CKD education and screening, free APOL1 genotyping.
2. Lack of awareness of therapeutic trial for kidney disease.	Engage and inform care providers and patients with clinical trial information.
3. The study site is a hassle to visit—it is far or requires too much time to access.	Use community-based research model. Meet participants where they are. Engage participants where they frequently congregate and feel most comfortable. Reimburse travel.
4. Implicit bias and inadequate cultural sensitivities.	Use culturally sensitive tools. Provide cultural sensitivity training for study staff.
5. Underrepresentation of African Americans and Black individuals among the research team.	The JUSTICE team reflects the target community: the principal investigator, coinvestigator, clinical research coordinator, and many of the study staff are African American or Black individuals.
6. Concern about potential health risk associated with participation in clinical trials.	Address the potential adverse effects of the investigational drug. Explain the rationale for a double-blind, placebo-controlled study design.
7. African Americans are not invited to participate in clinical trials due to the misconception that they are not interested.	Using culturally sensitive “just ask” approach, invite African Americans to participate in JUSTICE.
8. Distrust of medical research establishment due to history of exploitation and unethical research practices.	Acknowledge past problems. Describe safeguards to protect research participants. Invite and address participant’s concerns about medical research.
9. Discomfort with inherent uncertainty of trial participation.	Be transparent about potential personal health benefits and risks of participation.
10. Lack of access to a large population of potentially eligible African Americans.	Partner with African American community-based organizations, trusted influencers, and medical professionals that serve the African American communities.

## Methods

### Study Participants

Individuals aged 18 to 70 years, with biopsy-proven FSGS or clinically attributed HTN-associated CKD not due to diabetes, estimated glomerular filtration rate (eGFR) ≥25 ml/min per 1.73 m^2^ and albuminuria ≥300 mg/g, are eligible for the study if they carry APOL1 HRG. Inclusion and exclusion criteria are summarized in Tables 2 and 3. These individuals will be enrolled from clinics and the wider African American community through the Community APOL1 Research Engagement (CARE) registry (www.kidneycareandjustice.com). JUSTICE, as a part of the NEPTUNE observational study network,^32^ will also enroll participants from NEPTUNE. Individuals who self-report as Black or African American, Afro-Caribbean, Afro-Latino, or with recent African ancestry, between 18 to 70 years of age and residing in the United States are screened for history of high blood pressure, presence of albuminuria, reduced eGFR and presence of APOL1 HRG. It is possible that an individual with recent West African ancestry may be unaware of their geographical ancestry and may not self-identify as Black or African American. Therefore, if such individuals are known to carry APOL1 HRG, for instance through direct-to-consumer genetic testing, they will be eligible to screen for the JUSTICE trial, irrespective of racial or ethnic identity. It was recently reported that APOL1 G2 haplotype with a rare p.N264K single nucleotide polymorphism is protective against the risk of AMKD.^33^^,^^34^ Therefore, prospective participants with APOL1 genotypes of G1G2 or G2G2 with 1 or more p.N264K G2 haplotype will be ineligible to participate in JUSTICE. APOL1 genotype of participants entering JUSTICE is determined by using well-established Taqman based allelic discrimination or by Sanger sequencing.^21^

**Table 2 tbl2:** JUSTICE key inclusion criteria

1. The patient is willing and able to provide signed informed consent.
2. The patient resides in the United States.
3. The patient is male or female aged 18–70 years.
4. The patient has biopsy-proven FSGS or clinically diagnosed HTN-CKD
5. The patient has estimated glomerular filtration rate (eGFR) ≥ 25 ml/min per1.73 m^2^ (based on CKD-EPI Cystatin C) at screening.
6. The patient has urine albumin-to-creatinine ratio (UACR) ≥ 300 mg/g at screening.
7. The patient has high-risk APOL1 genotype of G1G1, G1G2, G2G2.
8. Patients taking antihypertensive medications must be on a stable regimen for at least 1 month prior to enrollment.

**Table 3 tbl3:** JUSTICE key exclusion criteria

1. The patient has diagnosis of diabetes mellitus.
2. The patient has biopsy-proven tip variant of FSGS.
3. The patient has history of kidney transplant.
4. The patient has sickle cell disease.
5. The patient has diagnosis of HIV or positive hepatitis B surface antigen.
6. The patient has significant liver disease with the most recent aspartate aminotransferase or alanine aminotransferase >1.5 times the upper limit of the normal range or the most recent available total bilirubin >1.5 times the upper limit of the normal range.
7. The patient has disqualifying laboratory abnormalities during screening, including hemoglobin <10 g/dl, absolute lymphocyte count <500 cells/mm^3^ or absolute neutrophil count < 1000 cells/mm^3^
8. The patient has systolic blood pressure ≥ 180 mm Hg or diastolic blood pressure ≥ 90 mm Hg.
9. The patient has current or prior history of treatment with a JAK Inhibitor.
10. The patient has active serious viral, bacteria, fungal or parasitic infection.
11. The patient has symptomatic herpes zoster infection within 12 weeks prior to study entry.
12. The patient has active malignancy.
13. The patient is pregnant, breastfeeding, or plans to become pregnant during the study period.
14. The patient, in the opinion of the investigator, is unable to comply with the requirements of the study.

FSGS, focal segmental glomerulosclerosis; JAK, Janus kinase.

### Sample Size and Power Calculation

In Table 4, we present sample size estimates, assuming 30%, 35%, and 40% differences between baricitinib and placebo, power of 80% or 85%, different SDs for percent change in UACR from baseline to the end of month 6, and the 2:1 active:placebo randomization scheme. For the purpose of the power calculation, we assumed 0% change in UACR in the placebo arm. Assuming the higher SD of 50%, a sample of 75 participants (50 in treatment arm and 25 in placebo arm) will provide 80% power to detect a 35% decrease in UACR at month 6 compared to placebo in the overall study population with a 2-sided significance level of 5%. A total of 25 patients with FSGS and 50 patients with HTN-associated CKD will be enrolled into the study. There will be no planned interim analyses although the Data Safety and Monitoring Board will have access to unblinded results at their regularly scheduled meetings. Approval of the study design and procedures was obtained from the Duke University Institutional Review Board before enrollment. Written informed consent is obtained for participation in the study.

**Table 4 tbl4:** Sample size and power calculation

Standard deviation	Difference	Power	Required Sample size		
			Total	Baricitinib	Placebo
SD = 0.33	0.30	80%	45	30	15
		85%	51	34	17
	0.35	80%	36	24	12
		85%	39	26	13
	0.4	80%	27	18	9
		85%	30	20	10
SD = 0.50	0.30	80%	102	68	34
		85%	117	78	39
	0.35	80%	75	50	25
		85%	87	58	29
	0.4	80%	60	40	20
		85%	66	44	22

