### Statistical Analyses

We will use standard descriptive statistics to compare clinical characteristics at baseline according to the treatment arm. The primary analysis will be a comparison of differences in percent change in UACR from baseline to month 6 across treatment arms in the overall study population using 2-sample t-tests. This primary analysis will be conducted according to the intention-to-treat principle with participants analyzed according to the treatment arm to which they were randomized, regardless of subsequent crossover or post-randomization treatment. In secondary analyses, we will compare the effects of baricitinib versus placebo on percent change in UACR within each of the APOL1 disease strata (FSGS and HTN) separately. In further analyses, we will assess the between-group and within-group changes in UACR using linear mixed models with visit number (baseline, months 1–6) representing the repeated-measures factor and randomization arm treated as a fixed-effect term. We will select the appropriate covariance matrix (e.g., compound symmetry, autoregressive, unstructured, etc.) based on the data to account for repeated observations. The statistical test for significant differences between the groups will be the time x group interaction that assesses the overall differences between groups in longitudinal UACR. The mixed model analyses will enable us to assess within subject changes in UACR over time, and to adjust for any imbalances in baseline factors that may occur in this relatively small study. We will use the same strategy involving linear mixed models to assess the effects of the intervention on eGFR and the chemokine biomarkers (CXCL9–11). For the primary assessment of safety, we will investigate the incidence of hemoglobin reduction by ≥1 g/dl in each arm and the mean change in hemoglobin from baseline to the end of study in each arm. We will also report adherence based on pill count data and use standardized methods to report all adverse events.

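### The 75 participants that 80% power requires are also the 75 to be randomised, so the power claim leaves no allowance for missing month-6 UACR

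*Protocol article*

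**What the plan says.** All of the following is in the Protocol article.

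- **Sample Size and Power Calculation.** The claim is that "a sample of 75 participants (50 in treatment arm and 25 in placebo arm) will provide 80% power". The target is a 35-point fall relative to placebo: "we assumed 0% change in UACR in the placebo arm". The SD is the larger of the two considered ("Assuming the higher SD of 50"%), and the test is run "with a 2-sided significance level of 5"%.
- **Table 4.** The row for SD 0.50, difference 0.35 and 80% power lists 75 in total (50 baricitinib, 25 placebo) as the required size.
- **Enrolment**, in the same section: "A total of 25 patients with FSGS and 50 patients with HTN-associated CKD will be enrolled into the study". That is 25 + 50 = 75.
- **Randomization and Intervention.** The planned split is 17 v 8 in FSGS and 33 v 17 in HTN-CKD, so 17 + 33 = 50 on baricitinib and 8 + 17 = 25 on placebo.
- **Statistical Analyses.** The primary comparison, by intention to treat, is of "percent change in UACR from baseline to month 6 across treatment arms in the overall study population using 2-sample t-tests". A linear mixed model using all visits is listed among further analyses, not as the primary test.

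The article states no loss rate, no inflation of the sample size and no replacement of participants.

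**The concern.** A required sample size from a complete-data formula counts participants who contribute an outcome. Here that count is also the number randomised, and the power is stated without condition. Treatment lasts six months. Each UACR value is the average of two first-morning samples taken at least two days apart, and the primary outcome is the value at the end of month 6. Some missing values are therefore plausible, and each one reduces the number behind the t-test.

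What is at stake is how the result is read. The Discussion says a meaningful reduction in proteinuria would support a phase 3 trial. If the trial finds no difference, readers will judge that against a stated 80% power. After ordinary loss, and at the article's own SD, the real figure would be lower.

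**Working it through.** **Inputs** (Sample Size and Power Calculation, and Table 4): difference δ = 0.35; SD σ = 0.50; two-sided α = 0.05; "the 2:1 active:placebo randomization scheme"; n₁ = 50, n₂ = 25. The loss rates below are my assumptions.

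**Formula.** For a pooled two-sample t-test, SE = σ√(1/n₁ + 1/n₂), the noncentrality is λ = δ/SE, and df = n₁ + n₂ − 2. Power is the probability that a noncentral t with these parameters falls beyond ±t(0.975, df).

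**Step 1: reproduce the plan's figure.**
- SE = 0.50 × √(1/50 + 1/25) = 0.50 × √0.06 = 0.1225.
- λ = 0.35/0.1225 = 2.858; df = 73; critical value 1.993.
- Power = 80.5%. The article's 80% is confirmed.

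**Step 2: is there slack in the 75?** The next 2:1 size down, 48 v 24, has SE = 0.50 × √(1/48 + 1/24) = 0.125, λ = 2.80, df = 70 and power 78.9%. So 75 is the smallest 2:1 total that reaches 80%. The same calculation gives all 12 rows of Table 4 exactly as minimum complete-data sizes, so no row contains an allowance for loss.

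**Step 3: a few losses.**

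| Evaluable (baricitinib v placebo) | Power |
|---|---|
| 50 v 25 | 80.5% |
| 49 v 25 | 80.2% |
| 48 v 25 | 79.9% |
| 50 v 24 | 79.4% |
| 49 v 24 | 79.1% |

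These are changes of about one point or less.

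**Step 4: larger losses, assumed equal in both arms.** Arm sizes are 50(1 − d) and 25(1 − d), with fractions kept. The last column solves for the δ that gives 80% power at σ = 0.50.

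| Loss d | Evaluable | λ | Power at δ = 0.35 | Difference detectable with 80% power |
|---|---|---|---|---|
| 0% | 50 v 25 | 2.858 | 80.5% | 34.8 points |
| 10% | 45 v 22.5 | 2.711 | 76.2% | 36.7 points |
| 15% | 42.5 v 21.25 | 2.635 | 73.7% | 37.8 points |
| 20% | 40 v 20 | 2.556 | 71.0% | 39.0 points |

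**Step 5: sensitivity to the SD.** With σ = 0.33, the lower value in Table 4, power at δ = 0.35 is 99.0% with no loss, 98.2% with 10% lost and 96.8% with 20% lost. The shortfall therefore belongs to the SD of 0.50 on which the article rests its claim.

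**The case against.** **Nothing is miscalculated.** This stands. A reader might infer from the point that Table 4 is wrong. It is not: every row reproduces, and the power sentence is true for 75 participants with complete data.

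**The claim does not collapse with the first missing value.** This also stands. It is tempting to say that 80% holds only if all 75 supply a month-6 UACR, or that a single placebo loss defeats it. Step 3 does not support that. Losing one baricitinib participant leaves 80.2%, and losing one placebo participant gives 79.4%, a difference that nobody should act on. The matter becomes material at roughly 10% loss, and the article gives no rate to say whether that will happen. Optional virtual visits from visit 3 onward may limit loss.

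**The full protocol or the SAP may deal with missing data.** This stands in part. The article does not say how a missing month-6 value enters the intention-to-treat t-test, and that detail can properly sit elsewhere; its absence is not the finding. Imputation would not restore all the lost information, however, and an SAP cannot add participants to a stated total that already equals the uninflated requirement.

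**The mixed model might recover power.** Possibly, but it is not the primary analysis, and the article gives no within-participant correlation from which to calculate its power. No figure for it can be quoted from this document.

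**This is a pilot trial planned at the more cautious SD.** This stands as context. A reader might conclude that the trial is underpowered. The document does not support that, because power remains above 95% at SD 0.33 even with 20% lost. But the article makes a formal power claim at SD 0.50, and the claim should be accurate at that SD.

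**Conclusion.** The point holds in limited form. The calculation is correct, but the evaluable number required equals the number randomised, so the unconditional 80% has no room for ordinary loss. At the article's own difference, SD and test, power is about 76%, 74% and 71% with 10%, 15% and 20% missing at month 6. The detectable difference moves from about 35 to 37, 38 and 39 points.

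These figures assume that the t-test uses only participants with a month-6 value, that loss is equal in both arms and unrelated to outcome, and that the true SD is 0.50. The loss rates are assumptions throughout. This is a fault in how the power is stated, not evidence that 75 is the wrong size for the trial.

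**What to change.** Keep 75. In Sample Size and Power Calculation, replace the unconditional statement with wording such as: with an SD of 50%, 80% power to detect a 35-point difference requires 75 evaluable participants (50 baricitinib, 25 placebo); if 10%, 15% or 20% have no month-6 UACR, power is about 76%, 74% or 71%. Label the loss rates as assumptions. Adding that power stays above 95% at an SD of 0.33 with 20% lost would give the balancing context.

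The cost is two or three sentences and a slightly less favourable headline figure. Enrolment, randomisation and the primary analysis do not change.
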